### Criteria for discontinuing or modifying allocated interventions

Participants are free to withdraw from the trial at any point. We will collect reasons for withdrawal from subjects who drop out of the trial.

Participants will not be able to switch groups once they have been randomised to the intervention or control arms, even if they request to do so. Using participants’ lists, the facilitators will ensure that participants remain in their designated groups.

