### Strategies to improve adherence to intervention

We will recruit ten to twenty game jam facilitators to support participants and to ensure all groups are able to meet the challenge of each step of the game jam protocol. The facilitators will be final-year medical students or medical interns interested in cultural safety research or game-based learning. We will train the facilitators during one month before the game jam to ensure that they will have the skills successfully to support the game jam participants in their learning process.

We will record the attendance to the intervention and control arms activities. Along with the names of the participants, we will record the date, hour, and their signatures.

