### Recruitment

We will contact the medical students and medical interns using *La Sabana* University’s mailing lists and will e-mail invitations for voluntary participation in the project. For those willing to participate, we will send further information about the project as well as the date and place of the intervention. We will ask interested students to complete the online informed consent and baseline questionnaire one week before the RCT.

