The instructions will make clear that participants should feel free to write down stories of negative changes or to say that they did not experience any change at all. Only medical students involved in clinical practice and medical interns (third to seventh year of medical school) will be invited to participate in this part of the RCT.

Methods to maximise completeness and quality of data: The study coordinator and facilitators will be physically present while collecting the data at each time point to ensure the completeness of data. Additionally, we will use several validation options to increase the quality of the data: specific number range, specific character range, date validation, email address format, and prompts that alert participants when they enter incomplete or invalid answers.

In this study, the familiarity of millennial medical students with technology and computer-based education supports using Web-based questionnaires, which reputedly decrease social desirability bias.[40] Assured of anonymity, respondents should be less concerned about what others may think about their responses, including peers and professors.[41] Data reliability in Web-based questionnaires is reportedly equal to or better than traditional paper-based approaches.[42] Examples include data on self-reported perceived health status, oral contraceptive use, and smoking and alcohol use. Web-based questionnaires are also faster to complete and typically cheaper than traditional approaches, making them ideal for our research.

Methods for ensuring secure storage of data: SurveyMonkey and Google responses are stored in a worksheet that can only be accessed through an account login. Data transmission uses Secure Sockets Layer to encrypt information during transport. The data storage is as secure as most other systems that store survey information. After downloading the data, we will delete it from SurveyMonkey and Google Forms. We will be responsible for ensuring the data are securely stored for seven years and then destroyed in accordance with CIET guidelines for security, storage, and eventual destruction of data records.[43]

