Missing data: There is no reason a priori to expect differential missing data between game jam and standard lesson groups, since both include a cultural safety educational intervention. We will document missingness and analyze missing data using Amelia II[48] to impute values for missing data with an EM algorithm for the primary outcome. Estimates will reconcile data from ten imputed data sets using Rubin’s approach[49] in the R package Zelig.[50] Additionally, we will provide an attrition diagram[51] (e.g., proportion of participants completing the surveys in each group plotted over time) demonstrating the engagement of participants over time.

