| Allocation concealment mechanism | 16b | Mechanism of implementing the allocation sequence (eg, central telephone; sequentially numbered, opaque, sealed envelopes), describing any steps to conceal the sequence until interventions are assigned | 19 |
| Implementation | 16c | Who will generate the allocation sequence, who will enrol participants, and who will assign participants to interventions | 18 |
| Blinding (masking) | 17a | Who will be blinded after assignment to interventions (eg, trial participants, care providers, outcome assessors, data analysts), and how | 19 |
|  | 17b | If blinded, circumstances under which unblinding is permissible, and procedure for revealing a participant’s allocated intervention during the trial | N/A |
| **Methods: Data collection, management, and analysis** | | |  |
| Data collection methods | 18a | Plans for assessment and collection of outcome, baseline, and other trial data, including any related processes to promote data quality (eg, duplicate measurements, training of assessors) and a description of study instruments (eg, questionnaires, laboratory tests) along with their reliability and validity, if known. Reference to where data collection forms can be found, if not in the protocol | 19 to 21 |
|  | 18b | Plans to promote participant retention and complete follow-up, including list of any outcome data to be collected for participants who discontinue or deviate from intervention protocols | 22 |
| Data management | 19 | Plans for data entry, coding, security, and storage, including any related processes to promote data quality (eg, double data entry; range checks for data values). Reference to where details of data management procedures can be found, if not in the protocol | 22 and 23 |
| Statistical methods | 20a | Statistical methods for analysing primary and secondary outcomes. Reference to where other details of the statistical analysis plan can be found, if not in the protocol | 23 |
|  | 20b | Methods for any additional analyses (eg, subgroup and adjusted analyses) | 23 and 24 |
|  | 20c | Definition of analysis population relating to protocol non-adherence (eg, as randomised analysis), and any statistical methods to handle missing data (eg, multiple imputation) | 24 |
| **Methods: Monitoring** | | |  |

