| **Development and pre-testing** | Development and testing | We will use a 30-item instrument comprised of three parts. The first part (five items) will explore sociodemographic factors of the students. The second part (15 items) will be based on the Transcultural Self–Efficacy Tool and will explore knowledge, attitudes, skills, and behaviors of cultural competence. For the third part of the instrument (cultural safety), we developed a Likert-type preliminary version based on our CASCADA variables (see primary outcome) and piloted it for validity and reliability in our pilot RCT.  Regarding the qualitative data, using a pre-defined format in Google forms, we will ask participants to write down and enter their stories. |
| **Recruitment process and description of the sample having access to the questionnaire** | Open survey versus closed survey | Closed survey sent by institutional email from *La Sabana* University. |
|  | Contact mode | Contact with participants online through e-mail and face-to-face. |
|  | Advertising the survey | Not applicable. |
| **Survey administration** | Web/E-mail | E-mail survey using SurveyMonkey and Google Forms. There was an automatic method for capturing responses. |
|  | Context | We will contact the medical students and medical interns using *La Sabana* University’s mailing lists and will e-mail invitations for voluntary participation in the project. |
|  | Mandatory/voluntary | Voluntary survey. |
|  | Incentives | Participants of the qualitative component of the study will enter a raffle after submitting their story. We will offer one gift card of CAD 20 for every ten stories collected. |
|  | Time/date | July 2019 to July 2020. |
|  | Randomization of items or questionnaires | Stratified randomization by cultural safety score at baseline. |
|  | Adaptive questioning | Not applicable. |
|  | Number of items | 30 items in total. |
|  | Number of screens (pages) | Three Webpage per survey. |
|  | Completeness check | We will use several validation options to increase the quality of the data: specific number range, specific character range, date validation, email address format, and prompts that alert participants when they enter incomplete or invalid answers. |
|  | Review step | Respondents were not able to review and change their answers. |

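### No outcome collection is planned for randomised students who miss or leave the session, so the intention-to-treat analysis may become an attenders' estimate

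*Protocol*

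**What the plan says.** All references are to the Protocol.

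- **Order of events.** Recruitment: "We will ask interested students to complete the online informed consent and baseline questionnaire one week before the RCT". Allocation stratifies on the baseline score, so randomisation comes after the online baseline and before the session. Results reports 640 students randomised.
- **Stopping.** Criteria for discontinuing or modifying allocated interventions: "Participants are free to withdraw from the trial at any point". It adds that reasons for withdrawal are collected. It does not mention students who miss or leave the session, or their outcomes.
- **Attendance.** Strategies to improve adherence to intervention: "We will record the attendance to the intervention and control arms activities".
- **Collection.** Data collection methods: "The study coordinator and facilitators will be physically present while collecting the data at each time point to ensure the completeness of data". The CHERRIES table in Multimedia Appendix 2 describes the mode as "E-mail survey using SurveyMonkey and Google Forms" and the contact as "Contact with participants online through e-mail and face-to-face".
- **Analysis.** Methods for analyzing data specifies an intention-to-treat t-test, within and between arms. Its missing-data paragraph uses Amelia II to "impute values for missing data with an EM algorithm for the primary outcome", with ten data sets and no list of imputation variables. The CHERRIES table, by contrast, restricts analysis to questionnaires that were completed.
- **Checklist.** SPIRIT item 18b, in its template wording "including list of any outcome data to be collected for participants who discontinue or deviate from intervention protocols", is given a page number. The text on completeness of data contains no such list.

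**The concern.** Consent and baseline are given online a week ahead, and the session is a voluntary full day. Some randomised students can be expected not to come, or not to stay. They belong in an intention-to-treat comparison, yet the only collection arrangement described for the outcome time points is one with staff in the room.

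The missing-data paragraph takes comfort from the fact that both arms receive teaching, so that differential loss is not expected. That reasoning does not cover students who received neither session. For them the expected difference between arms is about zero. If the outcomes of attenders stand in for theirs, the estimate moves away from the as-randomised effect even when both arms lose exactly the same share. At stake is what the headline result means: the effect of being offered a game jam, or the effect among those who took part.

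**Working it through.** **1. The collection texts side by side.** Staff presence at every time point cannot be literally true, because the baseline is completed online. The CHERRIES table allows e-mail contact. Neither text says whether a randomised non-attender is sent the post-session or six-month questionnaire, and no other section does.

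**2. The plan's effect size.** From Sample size: (26.9 − 25.9)/4 = 0.25, as stated; in points, a difference of 1.0 with SD 4. (The 199 per arm does not reproduce at two-sided 0.05 and 80% power. The normal formula gives 252, and 199 corresponds to a one-sided test. That is a separate matter and is not used below.)

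**3. Size of the shift.** Assume a share q of each arm does not attend, has no session effect and otherwise resembles the attenders. Then the as-randomised difference is (1 − q) × 1.0, the attenders' difference is 1.0, and the ratio is 1/(1 − q). The ratio does not depend on the effect size. The Protocol gives no q, so these values are assumed.

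| q | As randomised (points) | In SD units | Attenders (points) | Ratio |
|---|---|---|---|---|
| 5% | 0.95 | 0.2375 | 1.0 | 1.05 |
| 10% | 0.90 | 0.225 | 1.0 | 1.11 |
| 20% | 0.80 | 0.200 | 1.0 | 1.25 |
| 30% | 0.70 | 0.175 | 1.0 | 1.43 |

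If students who leave part-way keep half the effect, the ratio is smaller: at q = 20%, 1/(0.8 + 0.2 × 0.5) = 1.11.

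**4. Which analysis route produces it.** Simulation of 400 trials with 320 per arm (640/2) and 10 imputations from attenders. The baseline–outcome correlation of 0.5 and the control-session gain of 3 points are assumptions, so attenders in the game jam arm gain 3 + 1 = 4.

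| q | Arm in imputation model | Between arms: true → imputed | Game jam gain: true → imputed |
|---|---|---|---|
| 10% | yes | 0.91 → 1.01 | 3.61 → 4.01 |
| 10% | no | 0.92 → 0.92 | 3.60 → 3.95 |
| 20% | yes | 0.79 → 1.00 | 3.20 → 4.00 |
| 20% | no | 0.84 → 0.83 | 3.22 → 3.92 |

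- With arm in the model, the imputed between-arm difference is the attenders' difference.
- Without arm, there is no between-arm inflation. Leaving arm out shrinks the difference by the missing share, which here equals the share assumed to have no effect.
- The within-arm gain is overstated either way. At q = 20% the true gain is 0.8 × 4 = 3.2. Imputation gives 4.0 with arm, and 0.8 × 4 + 0.2 × 3.5 = 3.9 without. The plan counts nine within-group p values beside three between-group ones.
- Analysing completers only also targets 1.0, by exclusion rather than imputation.

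**5. Power if everyone is measured.** With 320 per arm, two-sided 0.05 and SD 4: 88.5% at full attendance, 81% at q = 10%, 72% at q = 20%.

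**The case against.** The strongest reply is that the sentence on staff presence is a safeguard for completeness and does not make in-person collection exclusive. The questionnaires are self-administered online and the CHERRIES table describes an e-mail survey, so absent students could be reached, most easily at six months. This stands in part. A reader might infer that students who never attend are certain to have no outcome; the documents do not establish that. They also do not say that such students will be asked.

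A reader might likewise infer that leaving the session counts as leaving the trial. The section on discontinuing interventions does not say so. It is silent, and what can be said is that the two events are not distinguished.

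The imputation variables are not stated and may be set out in a statistical analysis plan. Without arm in the model the between-arm inflation disappears, so that part of the point is conditional. Who is followed up, however, is a matter for the protocol. The completers-only statement conflicts with imputation altogether, but it leads to the same attenders' target between arms.

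Finally, no attendance figure is given. A reader might set the 640 randomised against the 400 planned and infer how many stayed away; nothing in the Protocol supports that. The promised attrition diagram will show how large the gap is, but will not correct it.

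**Conclusion.** The point holds as a conditional design gap that should be closed. Randomisation precedes the session, outcome collection is described as staff-attended, missing or leaving the session is not separated from withdrawing from the trial, and no outcome collection is planned for non-attenders, although a channel that could reach them exists.

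If they go unmeasured, the result labelled intention-to-treat targets the effect in attenders. The between-arm overstatement is 1/(1 − q), or 1.11 and 1.25 at assumed rates of 10% and 20%. It requires that non-attenders gain nothing and resemble attenders otherwise, that non-attendance is equal in the arms, and that either arm is in the imputation model or only completers are analysed. Within-arm gains are overstated under either imputation model. The actual size cannot be known from the Protocol.

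**What to change.** 1. In Criteria for discontinuing or modifying allocated interventions, separate not attending or stopping the session from withdrawing from follow-up. State that students in the first group remain in the trial and are asked for every outcome.
2. In Data collection methods, keep the on-site staff support and add that the post-session and six-month questionnaires are e-mailed to every randomised student in both arms, whatever their attendance.
3. Use the attendance record in the imputation, so that missing non-attenders are imputed from measured ones. If too few non-attenders respond for that, add a sensitivity analysis in which never-attenders are imputed with no arm effect.
4. Reconcile the staff-presence sentence with the e-mail survey in the CHERRIES table, and the imputation plan with that table's completers-only rule.
5. If post-session data have already been collected from attenders only, label that result an attenders' estimate and apply the rule to the six-month survey.

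The cost is protocol wording and e-mails through the institutional mailing already in use, with no extra participants. The downside is that some remote questionnaires may be less complete than supervised ones, and that the intention-to-treat estimate will probably be smaller, with the lower power shown in step 5 of the working.

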### Methods for analyzing data

Primary analysis***:*** using an intention-to-treat approach, we will perform a t-test including 95% confidence intervals to determine the effect of the intervention, including within-group comparisons (baseline and post-intervention I and II) and between-group comparisons (treated versus control post-intervention).

Secondary analysis: we will adjust for sociodemographic baseline variables. We will conduct both a logistic regression and the Mantel-Haenszel procedure, which will allow comparing the results using two different statistical approaches based on different assumptions. Contrary to logistic regression, the Mantel-Haenszel procedure is nonparametric, which makes it free of any statistical assumption and therefore more robust.[44]

Supplementary analysis: both intervention and control arms will engage in group work during the training session. We will use generalised linear mixed modelling (GLMM), paying special attention to a possible cluster enhancement as participants in some study groups generate stronger learning dynamics than others. Additionally, we will follow the methods proposed by [name] and collaborators[24] to conduct probabilistic transitive closure of each CASCADA result chain, which will allow us to explore walks and blocks between intermediate outcomes and to obtain the cumulative net influence. Probabilistic transitive closure is usually conducted on fuzzy cognitive maps where the weights of relationships between concepts are interpreted as probabilities.[45] Every relationship in the map contributes to the summary weight of a walk through a multiplicative function; this approach is appropriate when the number of factors of the model is pre-set.[45]

In our primary analysis, the between-group comparison will yield three *p* values, and the within group-comparison will yield nine *p* values. We will use the Holm procedure to adjust for multiple testing.[46] The Holm method is as robust as the Bonferroni method, but much more powerful.[47]

Non-statistical methods: the students will enter their narratives of change online. Using AtlasTi 8, two research assistants will individually analyze the transcripts following a deductive thematic analysis approach. In deductive analysis, a theory aligned with the researchers’ interest drives the data analysis;[35] we will use the steps described by the CASCADA model to identify themes of change in the stories.

Missing data: There is no reason a priori to expect differential missing data between game jam and standard lesson groups, since both include a cultural safety educational intervention. We will document missingness and analyze missing data using Amelia II[48] to impute values for missing data with an EM algorithm for the primary outcome. Estimates will reconcile data from ten imputed data sets using Rubin’s approach[49] in the R package Zelig.[50] Additionally, we will provide an attrition diagram[51] (e.g., proportion of participants completing the surveys in each group plotted over time) demonstrating the engagement of participants over time.

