Fowler and collaborators recently found that game jam participation could improve computing students' performance.[15] We are not aware, however, of any reported experience using game jams to train medical students. Our primary objective is to determine whether medical student participation in a game jam to design an educational game on cultural safety is more effective than a standard lesson on cultural safety in terms of change in students’ self-reported intended patient-oriented behavior. Our secondary objectives are to: (i) determine the impact of the intervention (game jam) compared with the control (standard lesson on cultural safety) on students’ confidence in their general transcultural skills; and (ii) assess the impact of participation in the game jam through a narrative approach that identifies in their own words the effect of the learning on cultural safety in their clinical practice.

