### Outcomes

Primary outcome: our primary outcome will be students’ self-reported intended patient-oriented behavior. Our outcome is self-reported because it uses students’ opinion regarding their perceived change; intended, because we are assessing students’ planned behavior instead of actual practice/action; and patient-oriented because we measure responses to clinical scenarios indicating intended behavior change. We will assess intended behavior change from the baseline to immediately following the teaching session, from immediately following the teaching session to six months post-intervention, and from the baseline to six months post-intervention.

We will use the CASCADA model of planned behavior to inform our primary outcomes.[22] The model includes the following variables: **C**onscious knowledge was the response to the statement: Considering the cultural beliefs of my patients is not important for health-decision making. **A**ttitude to cultural safety was derived from the statement: It is not worth considering the cultural beliefs of my patients to improve their health. **S**ubjective norm used the statement: Although many physicians disapprove cultural beliefs, I think that these beliefs could improve my patients’ health. Intention to **C**hange derived from the statement: I do not think that learning about cultural beliefs is necessary to provide good health care to my patients. **A**gency was the response to the statement: I feel prepared with the knowledge and skills to prudently incorporate my patients' cultural practices in the health-decision making process. **D**iscussion derived from the response to the statement: I will discuss cultural safety with other students and physicians so they can prudently incorporate their patients' cultural practices in the health-decision making process. Agency and Discussion replace perceived behavior in a conventional theory of planned behavior.[23] Agency involves both self-efficacy and collective efficacy. The CASCADA model includes Discussion as an additional factor that facilitates behavior change.[24] **A**ction was the response to the statement: I will never be open to include my patients’ cultural beliefs and practices in the health-decision making process. Participatory research experts have successfully used the CASCADA model to explore dengue prevention behavior in previous trials.[24]

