### Allocation

A potential source of bias in our study is a possible imbalance in the level of cultural safety training between the intervention and control groups before the intervention. The reason for this issue is that in Colombia around 40% of the population uses cultural and traditional practices to maintain their health.[28] Therefore, some students will be familiar with traditional health practices, probably making them more likely to embrace the cultural safety approach compared with students not familiar with these practices.

To address this potential bias, we will use stratified randomization by cultural safety score at baseline. Based on the preliminary results of the baseline survey, we will split the group of medical students into two groups: low and high level of cultural safety knowledge. Computerized randomization will allocate the students either to the intervention or control arm and we will use equal allocation between treatment arms. The study coordinator will be responsible for generating the allocation sequence, enrol participants, and assign participants to interventions.

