## Results

Study enrollment began in July 2019. 640 students completed the baseline survey and were randomised. Data collection is expected to be complete by July 2020 and results are expected in October 2020.

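### The primary between-arm t-test carries neither the baseline score nor the stratum used in randomisation, and the protocol leaves open whether the outcome is change or the post-intervention score

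*Protocol*

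**What the plan says.** **Objective and outcome.** The primary objective (Introduction, Transformative learning and game co-design) is to show that the game jam is "more effective than a standard lesson on cultural safety in terms of change in students’ self-reported intended patient-oriented behavior". The Outcomes section agrees: "We will assess intended behavior change from the baseline to immediately following the teaching session". It then adds two more intervals, from immediately after teaching to six months and from baseline to six months.

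**Analysis.** Under Methods for analyzing data, "we will perform a t-test including 95% confidence intervals to determine the effect of the intervention". The between-arm part is described as "between-group comparisons (treated versus control post-intervention". The same section states that "the between-group comparison will yield three" p values. The secondary analysis says "we will adjust for sociodemographic baseline variables", by logistic regression and Mantel-Haenszel. The mixed model is described only as a way to handle group-work clustering.

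**Sample size.** The effect size comes from pilot scores after teaching: means of 26.9 and 25.9, SD 4. These are not change scores.

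**Randomisation.** The Allocation section names prior cultural safety level as one possible source of bias and responds that "we will use stratified randomization by cultural safety score at baseline", split into low and high. The Results section reports that "640 students completed the baseline survey and were randomised".

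**The concern.** Two things are at stake.

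First, the protocol gives two different primary quantities. A t-test on change and a t-test on the post-intervention score estimate the same arm effect under randomisation, but they have different variances and will give different p values in the same data. If the choice is still open when the data are seen, there are two candidate primary results. The count of p values does not settle it. There are two post-intervention time points, so three p values fit either the three change intervals or three time points including baseline.

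Second, the design and the analysis do not match. Balancing the arms on a prognostic score reduces the true variance of the difference in means. An ordinary t-test does not know this and reports a standard error that is too large. The continuous score would also remove outcome variance within strata, and that precision is given up although the data are already collected.

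**Working it through.** **Inputs from the protocol.** Pilot means 26.9 and 25.9, SD 4, two-sided alpha 0.05, power 0.80, 199 per arm (Sample size); 640 randomised (Results), so 320 per arm at 1:1.

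**Assumptions.** The protocol gives no baseline-to-post correlation *r*, so 0.3, 0.5 and 0.7 are used. The low/high split is taken at the median of a normally distributed score, with equal allocation within each stratum. The stratifying score is taken to be the baseline value of the primary outcome.

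**Step 1: the plan's own figure.** d = (26.9 − 25.9)/4 = 0.25. Two-sided, n = 2(1.960 + 0.842)²/0.25² gives 252 per arm, not 199. One-sided, n = 2(1.645 + 0.842)²/0.25² gives 198, and the t-based one-sided calculation gives 198.5, hence 199. This is a separate matter. It explains why two-sided power at 199 per arm by the simple formula is 0.70 and not 0.80.

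**Step 2: change or post-score.** Relative to the post-score t-test, the variance of a change-score t-test is multiplied by 2(1 − r): 1.40, 1.00 and 0.60. Power at 199 per arm is Φ(2.494/√(2(1 − r)) − 1.960), where 2.494 = 0.25√(199/2). This gives 0.56, 0.70 and 0.90, against 0.70 for the post-score test. Both are by the simple formula without stratification. The two readings agree only at r = 0.5.

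**Step 3: the unadjusted post-score t-test under stratified allocation.** A median split of a normal score captures 2/π of its variance, so the true variance of the difference is k² = 1 − (2/π)r² times what the t-test assumes. Then:
- type I error = 2Φ(−1.960/k)
- power = Φ((λ − 1.960)/k), with λ = 0.25√(n/2), which is 2.494 at 199 and 3.162 at 320 per arm

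**Step 4: baseline-adjusted analysis.** Residual variance is multiplied by 1 − r² (0.91, 0.75, 0.51), and power = Φ(λ/√(1 − r²) − 1.960).

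| | r = 0.3 | r = 0.5 | r = 0.7 |
|---|---|---|---|
| k² | 0.943 | 0.841 | 0.688 |
| Type I error, unadjusted | 0.044 | 0.033 | 0.018 |
| Power at 199, unadjusted | 0.71 | 0.72 | 0.74 |
| Power at 199, adjusted | 0.74 | 0.82 | 0.94 |
| Power at 320, unadjusted | 0.89 | 0.91 | 0.93 |
| Power at 320, adjusted | 0.91 | 0.95 | 0.99 |

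Simulation agrees, with unadjusted type I error near 0.04, 0.03 and 0.02. With 199 people in each stratum one person is left over. If that person in the high stratum always goes to the game jam arm, simulated unadjusted power at 199 per arm is slightly higher, up to 0.76. Assigning the odd person at random returns 0.71 to 0.74. In a separate simulation at 199 per arm, the type I error of the adjusted test stayed near 0.05 (0.055, 0.045, 0.053).

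**Step 5: why adjustment settles most of the change question.** If Y₁ = a + τ·arm + βY₀ + γ·stratum, then Y₁ − Y₀ = a + τ·arm + (β − 1)Y₀ + γ·stratum. The arm effect τ is identical. This holds for change from baseline to either later time point. It does not hold for six months minus immediately after teaching, where the arm coefficient is the difference between two arm effects.

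**The case against.** The strongest reply is that an unadjusted t-test in a randomised trial is valid, so this is a matter of efficiency. Much of that stands. A reader might infer that the primary comparison is biased or prone to false positives. The documents do not support this: randomisation protects the comparison, and the error goes in the conservative direction. At r = 0.3 the loss is small. With 640 randomised, the unadjusted test exceeds 0.80 power before attrition, clustering and Holm adjustment.

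A reader might also infer that the protocol treats baseline imbalance as its chief threat. The Allocation section calls it only one potential source of bias. Nor does it say outright that the stratifying score is the same score as the primary outcome. That is likely, but inferred.

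It can also be said that the three p values point to the three change intervals, in which case baseline enters two of them by subtraction. That is possible. It contradicts the wording of the primary analysis, though, and subtraction is not adjustment: below r = 0.5 it costs power.

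Finally, covariate lists for secondary and mixed models are often left to a statistical analysis plan, so silence there is weak evidence. The finding does not rest on it. It rests on the primary test that the protocol does specify and on two statements of the primary quantity that disagree.

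**Conclusion.** The point holds as an unfixed estimand together with a primary test that does not match the stratified design. The consequences are lost precision and a conservative test, not bias. At 199 per arm the power lost by not adjusting is about 0.03, 0.10 and 0.20 for r = 0.3, 0.5 and 0.7. At 320 per arm it is about 0.02, 0.05 and 0.07. Choosing the change score over the post-score could move power at 199 per arm from 0.70 to anywhere between 0.56 and 0.90.

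The conflict between change and post-score follows from the text alone. The power and type I error figures rest on the assumed correlation, a median split, and a stratifying score that is the baseline of the primary outcome. If the cut is far from the median or the score differs, the loss from ignoring the stratum shrinks. This should be settled before the outcome data are analysed.

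**What to change.** - Name one primary time point. State the primary between-arm estimate as the adjusted mean difference at that time, with 95% confidence interval, from a linear model with arm, continuous baseline score and the low/high randomisation stratum. Use the same terms if the model is extended to carry group-work clustering.
- State that for outcomes measured from baseline this gives the same arm effect for change and for post-score, and use one description in the objective, Outcomes, Sample size and analysis sections.
- Label the change from immediately after teaching to six months as a separate secondary comparison. Make the number of between-group p values entering the Holm procedure match the comparisons listed.
- In the secondary analyses, add the baseline score to the logistic regression and use the low/high stratum in the Mantel-Haenszel procedure, since a continuous score cannot enter it directly. Note that adding the score changes the conditional odds ratio that the logistic model estimates.
- Training level is an optional covariate. It is not a stratification factor and is already among the sociodemographic variables.
- Say explicitly whether the stratifying score is the baseline value of the primary outcome.

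The cost is rewording and a modest change to the analysis code. No new data are needed, because completing the baseline survey preceded randomisation.
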